**Mobilisation of community and monitoring of project activities**

The entry point in the communities will be local leaders (village headmen and traditional authorities) and health surveillance assistants (HSAs). These are people who the community recognise as opinion leaders. The opinion leaders will be advised on the need for close consultation amongst themselves when mobilising the community or organising any activity. The structures that these people use to mobilise the people will be used to mobilise the communities. The community members will be involved in the development of the IEC materials. This will be done to ensure that the message is clear and is culturally acceptable by the community. Pre-testing of the messages will be also be done with the community to check the meaning and acceptability from the community’s perspective.

The district health office (DHO) will be playing advisory role during implementation of the project. Staff from the DHO will form part of facilitating team during training of informal healthcare providers. Since the intervention activities will be taking place in the DHOs area of jurisdiction, the officers will be involved at every step of the project development and implementation. As such, the HSAs at every health facility will be supporting REACH Trust staff in monitoring the project activities in the health facility catchment area.

**Project period**

The project is expected to run for five years (56 months; May 2008 – December 2012). The first two years will be for planning and setting up and the actual intervention will start in the third year.

**Project site**

The project will be implemented in rural parts of Lilongwe district. Ideally, the study region would be divided into “clusters”, each consisting of geographically delineated area (defined by a combination of at least 2 traditional authorities). The clusters would then be randomised to either receive the intervention (Early intervention arm) or to act as a control, (Delayed intervention arm) using stratification methods to ensure that the two sets of clusters would be as similar as possible in terms of their poverty profile, population structure, health service coverage, and presence of significant number of at least one of the selected community-based health care providers (store-keepers, ante-natal care clinic and home-based care organisations).

The problem with this methodology is that people in the study clusters do not always attend their “local” health centre, so there would be considerable problems of “pollution” between the two study groups, in that people living in intervention clusters would attend control cluster health centres, and vice versa. While it would be technically relatively simple to identify the location of participants’ homes (and hence do an “intention-to-treat” analysis with individuals assessed according to their actual residence address rather than health centre attended), this would not eliminate the likelihood that some people resident in control clusters would be exposed to the intervention and some people resident in intervention clusters would not be exposed to it. The decision was thus taken to divide the rural parts of Lilongwe district into just six groups with large population sizes of at least 166,000. A random number will be generated in Excel to determine which clusters will receive the intervention early and which will ones will receive the intervention later. Thus, the six study clusters will equally be randomised to the Early intervention arm (to receive the intervention early in the first 12 months) and the Delayed intervention arm (to receive the intervention after 12 months). The 6 clusters will be pair-matched according to population sizes and their proximity to the urban areas.

Because the intervention is to be implemented at community level, allocation of the intervention will not be blinded to the communities and the research team implementing the intervention. However, allocation of TB and HIV cases to the clusters will be blinded.

**Research packages**

The purpose of the research component of the project is to assess feasibility and measure effectiveness of the intervention package. The research will be done based on the pre-determined indicators and processes as outlined in the sections that follow.

**Project indicators**

Effectiveness will be measured by comparing quantitative health impact indicators for TB and HIV over the implementation period of Triage-Plus. The demographic and health survey (DHS) report of 2004 used the following defining characteristics and impact indicators: basic population; age composition and structure; gender, level of education, TB, HIV and poverty prevalence. Other indicators will be the number of cases identified, the proportion of cases put on single treatment and the proportion cases put on dual treatment. The same impact indicators will be measured in this study at baseline and on- going till the end of the project in both clusters (i.e. where Triage-Plus is and is not implemented). In this way the intervention is both historically and concurrently controlled.

There is a strong recognition that Triage-Plus is, however, a health system intervention, not a new drug. Therefore the methodology incorporates adaptations and additions to the clinical trial approach such as health economics and qualitative process evaluation. The former to analyse the cost effectiveness of the intervention to patients, informal healthcare providers and the formal health system and the latter to document the multiple changes, processes and to provide the context for the trial findings. In addition, an overarching strategy for the whole research process will be continuous involvement of the research partners, participation of the communities involved in the research, and engagement of those who need and will use the research results.

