Thus, assuming that actual TB cases are not rising in the community year on year, the expected number of smear positive TB cases registering for treatment in each study group over a one year period would be (329 / 2 =) 165, with at least as many smear negatives and other forms of TB. As this constitutes 55% of all smear positive TB cases, the actual number of smear positive TB cases occurring in each study group will be (165 / 0.55 =) 300. This will provide 87.5% power to detect an increase in the number of smear positive TB cases registering for treatment from 165 (55%) in the control group to 210 (70%) in the intervention group. Given that 41% of the TB cases were smear positive (WHO, 2009), then 512 TB cases (all forms of TB) were expected to start TB treatment at the end of the intervention in the intervention arm.

- - - - 1. HIV

*Primary outcome measure*: number of HIV-infected patients starting ART – the expected proportion of HIV-infected patients starting ART in this region of Malawi is currently estimated to be 15% - an increase in this proportion to 18% (a 20% proportional increase) in the intervention group would be considered clinically significant.

The population of Malawi is approximately 11 million, of which (approximately) 1.1 million (10%) live in the rural areas of Lilongwe. Estimates taken from Malawi’s 5 year ART Scale-Up plan indicate that 85,000 new patients become eligible for ART each year across the country, so 8,500 new patients become eligible for ART in the rural areas of Lilongwe. Data collected by the REACH Trust indicate that the ART programme starts 1,300 people on treatment in the Lilongwe rural health facilities per year, a treatment initiation rate of (1300 / 8500 =) 15%. Thus, the number of new patients becoming eligible for ART in each of the two study groups will be 4,250. This will provide 86.9% power to detect a 20% increase in the proportion of eligible patients starting ART (in absolute terms, from 15% in the control group to 18% in the intervention group).

It is hoped that the intervention will have a much greater impact on the primary outcome measure, increasing the proportion of eligible patients starting ART in the intervention group well towards the national target figure of 50%.

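### The effectiveness definition claims concurrent control to project end, but the delayed arm starts after 12 months; the primary comparison should be tied to those 12 months

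*Protocol*

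**What the plan says.** Under Project indicators the protocol states: "Effectiveness will be measured by comparing quantitative health impact indicators for TB and HIV over the implementation period of Triage-Plus". The indicators are to be measured at baseline and then "till the end of the project in both clusters (i.e. where Triage-Plus is and is not implemented". The section concludes: "In this way the intervention is both historically and concurrently controlled".

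Under Project site, six clusters are randomised equally to an early arm, treated within the first 12 months, and a delayed arm "to receive the intervention after 12 months".

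Under Project period, the project lasts 56 months, May 2008 to December 2012, and "The first two years will be for planning and setting up and the actual intervention will start in the third year".

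Under Data collection process, the TB sample size counts smear-positive cases "registering for treatment in each study group over a one year period". The HIV calculation uses the annual number of newly eligible patients. The Data analysis section plans incidence rate ratios and Poisson regression and names no counting period.

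**The concern.** Once the delayed arm starts, every study cluster has Triage-Plus. The Project indicators description of areas with and without the intervention, and the concurrent control it is said to give, therefore cannot hold to project end. It holds for the first 12 months only.

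The primary outcomes are numbers of patients starting treatment, compared as rate ratios, so the counting window is part of the endpoint. Implementation in the delayed arm begins only after month 12, so on its ordinary meaning the implementation period runs past crossover. An analyst who followed that wording would count treated time in the delayed arm as control time, and the rate ratio would move towards 1. The sample size section implies a different window of one year. If this were still open at analysis, the window could be chosen with results in view, and the protocol says the team implementing the intervention is not blinded to allocation.

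**Working it through.** **Inputs from the protocol.** TB: 55% versus 70% starting treatment, 300 smear-positive cases per arm, stated power 87.5%. HIV: 15% versus 18% starting ART, 4,250 eligible patients per arm, stated power 86.9%. Alpha is 1%. The project lasts 56 months, with the intervention starting in year 3 (months 25 to 36) and the delayed arm after 12 months.

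**Step 1. Reproduce the stated power.** A two-sided comparison of two proportions at alpha 1% gives 89.1% (TB) and 87.5% (HIV). With a continuity correction it gives 87.5% and 86.9%, matching the protocol. The stated power therefore belongs to one year of cases with a fully untreated control arm.

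**Step 2. Time available.** If the intervention starts at the beginning of year 3, 56 − 24 = 32 months remain. If it starts at the end of year 3, 56 − 36 = 20 months remain. With crossover right after month 12, both arms are treated for 32 − 12 = 20 or 20 − 12 = 8 of those months, that is 62.5% or 40% of the time.

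**Step 3. Ratio if the arms are compared over the whole period.** Let R be the true ratio and T the months from early-arm roll-out to project end. With constant rates and an immediate full effect, the delayed arm averages [12 + R(T − 12)]/T times the control rate, and the early arm has R times the control rate. The observed ratio is

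R × T / [12 + R × (T − 12)].

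TB, R = 70/55 = 1.273:
- T = 32: 40.73 / 37.45 = 1.09
- T = 20: 25.45 / 22.18 = 1.15

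ART, R = 18/15 = 1.20:
- T = 32: 38.4 / 36 = 1.07
- T = 20: 24 / 21.6 = 1.11

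The share of the planned absolute difference that survives is 12/T, which is 37.5% (T = 32) or 60% (T = 20).

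**Step 4. Power over the whole period.** The delayed-arm proportion is (12/T) × control + (1 − 12/T) × intervention, and the number of cases is scaled up by T/12. The figures use the formula without continuity correction and ignore clustering, as the protocol's own figures do.

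| Window | TB proportions | TB power | ART proportions | ART power |
|---|---|---|---|---|
| 12 months | 55% v 70% | 89.1% | 15% v 18% | 87.5% |
| 20 months | 61% v 70% | 66% | 16.2% v 18% | 61% |
| 32 months | 64.4% v 70% | 43% | 16.9% v 18% | 37% |

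The extra cases from a longer window do not make up for the smaller contrast.

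**The case against.** The strongest reply is that the protocol never plans a diluted analysis, and much of it stands.

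- Indicators are measured to project end. The comparison is in a different sentence, whose period has no stated end. Auditing registers after crossover biases nothing and can serve the historical comparison.
- The design and sample size sections agree on 12 months. The 512 TB cases of all forms expected at the end of the intervention in the intervention arm are 210/0.41 = 512, a one-year count.
- The indicators listed are partly general population characteristics, while the primary outcomes are defined in the sample size section.
- An exact analysis window is commonly left to the SAP, which is not at hand and may fix it.

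A reader might therefore infer too much: that the protocol commits itself to comparing the arms to December 2012 with treated delayed-arm time counted as control, and so to losing about two-thirds of the effect. The documents do not support that. No section prescribes such pooling, and the contrast by where Triage-Plus is and is not implemented sits badly with it. The two-thirds figure also needs the earliest possible start in year 3.

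The reply does not remove the contradiction. Measurement to project end is presented as what gives concurrent control, and under the protocol's own roll-out it cannot give that after month 12. This is a statement the protocol makes, not a detail it leaves open. The list of indicators also includes cases identified and proportions put on treatment, so the section is not remote from the primary outcomes.

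**Conclusion.** The point holds as an inconsistency in the effectiveness definition. Concurrent control is claimed without limit but exists only until the delayed arm starts. The one-year sizing implies a 12-month comparison, but no sentence in the protocol ends the comparison there.

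The size depends on which reading is followed. Under a 12-month comparison the loss is zero. Over the whole implementation period, the TB ratio falls from 1.27 to between 1.15 and 1.09 and the ART ratio from 1.20 to between 1.11 and 1.07, so 40% to 62.5% of the planned absolute difference is lost. These ranges assume a start anywhere in year 3, crossover right after month 12, an immediate full effect in both arms and constant rates. A slower effect or later roll-out in the delayed arm would reduce the dilution. This should be settled before the analysis, because the definition as worded would bias the primary result if followed.

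**What to change.** Amend Project indicators to agree with Project site and the sample size section, and repeat the statement under Data analysis:

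- The primary between-arm comparison counts TB and ART treatment starts, by date of start, only in the 12 months after roll-out in the early arm and before roll-out in the delayed arm.
- Concurrent control is claimed for that period only.
- Data from after delayed-arm roll-out are secondary, used either as a before-after description or in a model with terms for calendar time and current intervention status.

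The cost is a sentence or two. Data collection and field work stay the same, no data are discarded, and the primary comparison then matches the one-year basis of the stated power.

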With a decision to use six large clusters with at least 166,000 population to minimise pollution of the intervention, a proper sample size calculation using simulations will be implemented to guide the analysis plan. The simulation studies will be carried out before the analysis of the study.

*Data collection tools*

Data collection tools for primary and secondary outcome measures

Prior and subsequent to the intervention, the chronic cough registers, TB treatment registers, HTC and ARV Treatment Registers from health facilities in the whole of Lilongwe District (rural and urban) will be audited for patient numbers by health centre catchment area. These data will form the basis for the trial analysis. Place of residence data are crucially important in this study, so that the study staff can locate patients to traditional authorities and health centre catchment areas that are identifiable within either the intervention or the control area. The study staff will, therefore, conduct initial training and continuing quality assurance checks on these registers throughout the study.

Data collection tools for health economic evaluation

A questionnaire survey will be carried out on a random sample of 166 rural new smear positive TB patients (83 at each site) who have registered for treatment (or both) and 200 rural patients who have recently (within last 2 months) registered for ART at the beginning of the intervention and at the end of the trial period. A patient who has both started treatment for smear positive TB and who is registered for ART will count for both samples, therefore the total sample size may be less than 366. These surveys will capture HIV and TB patients’ pathways to care and collect data on individuals’ household assets and on health-seeking experiences around current symptoms, identifying where and why care was sought (appendix 4). Using a cost-effectiveness check-list data will be collected on staff, consumables, transport and other costs incurred by the health service in this intervention.

Data collection for process evaluation

Throughout the duration of the project, detailed monthly reports will be compiled and all minutes will be recorded. All individuals and organisations involved, their roles and their processes of engagement will be documented. Key informant interviews. Semi-structured interviews and in-depth interviews will also be done.

*Data analysis*

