Qualitative data will be transcribed verbatim. The transcribed data will be saved as rich text file (RTF) format which will be imported in MAXQDA. It will be organised according to themes for analysis.

The quantitative data will be collected and stored using pre-prepared Excel, Access and/or EpiInfo software databases. The characteristic of the control and intervention groups will initially be summarised and compared using standard univariate statistical methods (Fisher exact test and Student t-test/Mann-Whitney U-tests for categorical and continuous measures respectively). Effect sizes for the primary and main secondary measures will be summarised using incidence rate ratios with their 95% confidence intervals. Poisson regression methods will be used to investigate in greater detail the factors influencing the two primary outcome measures, and to adjust the effect estimates for confounding factors. The analyses will be conducted using the SPSS and Stata statistical packages at the REACH Trust, with supervision and advice as necessary provided by [name] (Senior Lecturer in Medical Statistics, Liverpool School of Tropical Medicine).

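### The protocol claims historical as well as concurrent control, but its stated effect estimate does not specify any use of the pre-intervention cluster rates

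*Protocol*

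**What the plan says.** **Baseline data and the control claim.** Under Project indicators the protocol says: "The same impact indicators will be measured in this study at baseline and on- going till the end of the project", in areas with and without the package. It concludes: "In this way the intervention is both historically and concurrently controlled". Under Data collection tools the source is "Prior and subsequent to the intervention, the chronic cough registers, TB treatment registers, HTC and ARV Treatment Registers from health facilities" across the district, with patients counted per catchment area. That section adds that these data are what the trial analysis will rest on.

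**The comparison.** Project indicators also says: "Effectiveness will be measured by comparing quantitative health impact indicators for TB and HIV over the implementation period of Triage-Plus". Under Data analysis: "Effect sizes for the primary and main secondary measures will be summarised using incidence rate ratios with their 95% confidence intervals". Poisson regression is then to be used to study influences on the two primary outcomes and "to adjust the effect estimates for confounding factors". The confounders are not listed. No baseline rate, change from baseline or arm-by-period term is named.

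**The design.** Under Project site, "the six study clusters will equally be randomised to the Early intervention arm" or the Delayed arm, three to each. Pairs are formed on population size and closeness to urban areas. Baseline TB or ART initiation rates are not matching factors.

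**Cluster variation.** No between-cluster variation is given. The section on sample size defers a cluster-based calculation to simulations, to be run before the analysis and to inform the analysis plan.

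**The concern.** Measuring a baseline does not by itself give historical control; the estimator has to use it. The protocol asserts the design property and then states an estimator that does not commit anyone to delivering it.

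With three clusters per arm, randomisation cannot be relied on to balance the outcome rates, and the matching helps only as far as size and urban proximity predict those rates. If the clusters differ appreciably before the trial, a comparison of follow-up rates alone carries that difference as noise, which may be as large as the effect sought. The pre-intervention rates that could remove part of it are already to be collected.

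Leaving open whether and how they are used also leaves room to choose between adjusted and unadjusted results after the data are seen. In a six-cluster trial that choice could decide the conclusion.

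**Working it through.** **1. The plan's own figures.** Inputs from the sample size section: TB 55% v 70% with 300 per arm; ART 15% v 18% with 4,250 per arm; alpha 1%. The stated powers reproduce with a two-sided, continuity-corrected comparison of two proportions, power = Φ[(d − 1/n − 2.576·SE0)/SE1], where SE0 uses the pooled proportion and SE1 the separate ones:
- TB: (0.1467 − 2.576 × 0.03953)/0.03905 = 1.148, power 87.5% (stated 87.5%).
- ART: (0.02976 − 2.576 × 0.008052)/0.008045 = 1.122, power 86.9% (stated 86.9%).

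Neither calculation contains a between-cluster term, so no k can be recovered from them. The targets as rate ratios are 0.70/0.55 = 1.27 (log 0.241) for TB and 0.18/0.15 = 1.20 (log 0.182) for ART.

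**2. Chance imbalance from clusters alone.** With three clusters per arm, the SD of the log rate ratio due to cluster differences is k·√(2/3). The chance of a difference at least as large as the target, in either direction and with no intervention effect, is 2[1 − Φ(log target / SD)]. Here k is assumed, Poisson variation is left out, and no credit is given for matching.

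| k | SD (as ratio) | TB | ART |
|---|---|---|---|
| 0.10 | 0.082 (1.09) | 0.3% | 2.6% |
| 0.15 | 0.122 (1.13) | 4.9% | 13.7% |
| 0.20 | 0.163 (1.18) | 14.0% | 26.4% |
| 0.25 | 0.204 (1.23) | 23.7% | 37.2% |
| 0.30 | 0.245 (1.28) | 32.5% | 45.7% |

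One SD equals the target at k = 0.241/0.816 = 0.295 for TB and 0.182/0.816 = 0.223 for ART.

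**3. What the baseline could buy.** Let s² = ln(1 + k²) be the between-cluster variance of log rates, ρ the share of it that persists from baseline to follow-up (assumed), and c the events per arm per year at the control rate: 165 for TB and 4,250 × 0.15 = 637.5 for ART. With one baseline year:
- follow-up only: variance V = (2/3)s² + 2/c
- raw change in log rate: variance 2[(2/3)s²(1 − ρ) + 2/c]
- observed correlation of cluster rates, Poisson noise included: R = ρs²/(s² + 3/c)
- log baseline as covariate, slope treated as known: variance V(1 − R²)

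| k, ρ | Outcome | R | SE follow-up only | SE change | SE covariate |
|---|---|---|---|---|---|
| 0.25, 0.9 | ART | 0.84 | 0.209 | 0.120 | 0.115 |
| 0.25, 0.9 | TB | 0.69 | 0.229 | 0.180 | 0.165 |
| 0.25, 0.5 | ART | 0.46 | 0.209 | 0.216 | 0.185 |
| 0.25, 0.5 | TB | 0.38 | 0.229 | 0.254 | 0.212 |
| 0.10, 0.9 | ART | 0.61 | 0.099 | 0.087 | 0.078 |
| 0.10, 0.9 | TB | 0.32 | 0.137 | 0.160 | 0.130 |

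The change score gains only where R exceeds 0.5. The covariate column is a best case, because six clusters estimate a slope poorly.

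**4. Degrees of freedom.** Treating the clusters as unpaired leaves 6 − 2 = 4. Analysing three pair differences leaves 3 − 1 = 2. A fitted covariate slope takes one more from either.

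**The case against.** The strongest reply is that silence is not exclusion. A reader might infer that the plan discards its baseline data. The documents do not support that: the confounder list is open, no baseline term is ruled out, and the protocol says the before-and-after register data underlie the trial analysis. The covariate list is also commonly left to a statistical analysis plan, which is not shown here. This stands as a limit on the wording. It does not remove the point, because the protocol itself claims historical control and itself states the estimator, and the two are not connected.

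A reader might also infer that a large imbalance is to be expected and will be reported as an effect. That is not supported either. The size depends on a k the documents do not give, it is rare at k = 0.10, and matching may reduce it. An interval that respects clustering already allows for chance imbalance in a randomised comparison. Whether the planned Poisson interval does so is a separate question. What baseline use adds is mainly precision.

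Finally, adjustment can cost precision. At k = 0.10 and 90% persistence, a raw change score raises the TB standard error from 0.137 to 0.160. At k = 0.25 and 50% persistence, it raises both outcomes. This stands, and it argues against fixing a change score as primary before the simulations.

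**Conclusion.** The point holds in this form: the protocol claims historical control and collects the data for it, but the stated effect estimate does not specify their use, and the matching is not on the outcome rates.

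Target-sized chance differences are a material risk for k from about 0.15 upward and unlikely for TB at k = 0.10. The potential gain is large if cluster rates are stable: at k = 0.25 and 90% persistence the ART standard error falls from about 0.21 to 0.12 and the TB one from about 0.23 to 0.18. It can be nil or negative for a raw change score if they are not. Both k and the persistence are assumptions. The text question is settled from the protocol; the size is not. This should be corrected, but it does not show that the trial's comparison is biased.

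**What to change.** In Data analysis, name the pre-intervention cluster rate in the primary analysis of both outcomes. Two forms are suitable: the log baseline rate as a covariate, or an arm-by-period (difference-in-differences) contrast. Either should be done at cluster level, or with a method that respects clustering, and with small-sample degrees of freedom consistent with the pair-matching. Use as many pre-intervention months as the registers give, since more baseline events reduce the Poisson noise that limits the TB gain.

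Choose between the forms in the simulations the protocol already promises, over a stated range of k and persistence, and fix the choice before outcome data are seen. Report the follow-up-only ratio as a sensitivity analysis.

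The cost is wording and some added simulation settings; no new data collection is needed. The statistical price is the possible loss of precision with a raw change score when the observed correlation is below about 0.5, or one degree of freedom and a poorly estimated slope with a covariate.
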